## Assignment of interventions: blinding

### Who will be blinded {17a}

Trial participants, care providers, outcome assessors, and data analysts are blinded, respectively, by using placebo group, by using site investigators to provide placebo or drugs to participants, by using blinded clinicians to assess the clinical outcome and laboratory or radiological findings, and by using analysts from other institution that are not having any conflict of interest in research. The details will be announced after locking the data in a database sheet at the end of the trial.

The study experimental drug and placebo will be prepared by the team of pharmacists and pharmacologists in the Department of Pharmacology and Toxicology, University of Veterinary and Animal Sciences, Lahore, Pakistan. Both drugs will look alike, as they will have same packing but unique randomization codes. Participants, site investigators, care providers, outcome assessors, study coordinators, data managers, and statisticians will be blinded, and blinding codes will be revealed at the end of this study.

### Procedure for unblinding if needed {17b}

Unblinding is permissible if the patient develops severe symptoms and needed extra treatment by revealing a participant’s allocated intervention during the trial. If unblinding is required, the trial managers and data coordinators will have access to group allocations and any unblinding will be reported.

## Data collection and management

### Plans for assessment and collection of outcomes {18a}

Microsoft Access, a database management system (DBMS) of Microsoft Office, will be used to ensure the data safety. SARS-CoV-2 RT-PCR test and HRCT score will be done every fourth day while COVID-19 symptoms evaluation will be done on daily basis to access the time taken for the alleviation of symptoms. Thirty-day mortality will be assessed by the number of deaths per group after 30 days of randomization in all groups. All trial data will be collected by site investigators and two site investigators will enter the data, recheck twice for possible errors separately, and make certain its integrity. Pre-approved questioner regarding demographics of the patient and data collection will be used while all the testing will be done by International Organization for Standardization (ISO) certified laboratory (Shaukat Khanum Laboratory). Principal investigators will visit twice weekly the study site. Trial steering committee members will make unexpected and unplanned visits as well. There is no conflict of financial and non-financial interest with sponsors and researchers.

### Plans to promote participant retention and complete follow-up {18b}

All the participants will be ensured their safety and will be guided about the study conduction and its beneficial outcomes. This study will be conducted till the patients hospitalized or home-quarantined in homes test negative for SARS-CoV-2 RNA in two consecutive nasopharyngeal swabs done using RT-PCR. All the data will be collected while the patient is already admitted in the hospital except 30-day mortality. Contact numbers and addresses of all participants will be reported at the start of study for which can be used, if needed, after written consent is obtained from the patient. Follow-up will be done using phone numbers of the patients to access the mortality benefit of intervention.

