**Discussion:**

The study is designed to measure the superior efficacy of the iodine complex as an add-on in treating COVID-19-positive patients with mild to moderate symptoms. This combination is hypothesized to improve various parameters like rapid viral load reduction, clinical and radiological improvement, lower mortality, and reduction in hospitalization. The trial will aid in devising a better strategy to cope with COVID-19 in a relatively inexpensive and accessible way. The implications are global, and this could prove itself to be the most manageable intervention against COVID-19 especially for patients from limited-resource countries with deprived socioeconomic status.

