### Intervention description {11a}

In this multi-armed study, ionic-iodine polymer complex will be given using three formulations with 200 mg of elemental iodine to evaluate efficacy for a maximum of 14 days or when the patient is fully recovered.
Arm A will be receiving 200 mg iodine complex capsule three times a dayArm B will be receiving iodine complex suspension syrup form 40 ml three times a dayArm C will be receiving iodine complex nasal spray 2 puffs three times a day.Arm X will be receiving a placebo of empty capsule three times a day.

All patients will receive standard care as per version 3.0 of clinical management guidelines for COVID-19 established by the Ministry of National Health Services of Pakistan COVID-19 guidelines of the study setting.

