### Strategies to improve adherence to interventions {11c}

To improve adherence to the intervention, participants will be counselled about the advantages of this study. All the participants will be monitored regarding compliance to their assigned treatment strategy and health professionals will administer the drugs. As this trial will include quarantined patients, hence direct observational method will be sufficient to make sure compliance and adherence to the interventions.

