### Outcomes {12}

Primary outcomes will include time to SARS-CoV-2 RT-PCR clearance, alleviation of symptoms, and better high-resolution computerized tomography (HRCT) chest score. Thirty-day mortality will be used as a secondary outcome. SARS-CoV-2 RT-PCR will be done on admission day (0 day) and then after every 4th day for 12 days or till the symptoms are resolved and RT-PCR gets negative. Symptom resolution is defined by the resumption of mild to moderate symptoms COVID-19 symptoms (defined by the definition of symptoms). RT-PCR will only be shown as positive or negative (as a limitation of our study of not getting the viral load). Time taken for the alleviation of symptoms will be measured as the number of days the patient remained symptomatic, i.e., the difference between onset of COVID-19 symptoms to complete resolution. HRCT chest scoring will be done as follows: Lungs divided into five lobes and each lobe is scored as 0 (no involvement), 1 (< 5% involvement), 2 (up to 25% involvement), 3 (26–49% involvement), 4 (50–75% involvement), and 5 (> 75% involvement). The overall HRCT chest score will be from 0 (no involvement) to 25 (maximum involvement) [16]. The HRCT findings are described via standard international terms, which are classified by the Fleischner Society glossary with peer-reviewed literature on viral pneumonia. The terms being used are ground glass opacity (GGO), crazy-paving pattern, and consolidation [17, 18]. Like a previous study [19], a maximum of 4 HRCT chest will be performed starting from day 0 followed by every fourth day till patients’ PCR become negative.

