### Sample size {14}

Considering it a novel idea to use iodine in the management of COVID-19, no software was used to calculate the sample size (Fig. 2). However, arbitrarily 50 patients in each arm with a total of 200 patients sample size for a multi-centered study in Pakistan will be randomized. In this adaptive trial, sample size reestimation is planned to achieve the study objectives, if needed. Time taken for the elevation of the symptoms will be considered as relevant endpoint (RE) while SARS-CoV-2 RT-PCR clearance and HRCT chest score will be studied as additional endpoints (AE). The required sample size will be calculated with 0.05 alpha and 80% power of the study.

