### Interim analyses {21b}

The risk aptitude for this study is customized as low risk, considering the use of nutraceutical product. However, as it involves vulnerable COVID-19 patients and novel drugs are being tested for repurposing, strict safety measurements will be taken. As a part of our safety measurements, the investigator, [name] (Professor of Cardiology, SZH, Lahore), with the biostatistician, [name]. [name] (Dean faculty of biostatistics, UVAS, Lahore), will conduct an interim analysis. The prime focus of this analysis will be mortality and incidence of any serious adverse effects. This will be carried out after randomization and inclusion of half of the patients. For these specific outcomes, those conducting the interim analysis will be unblinded. No stopping rules for the primary endpoint have been defined as this is the first trial of its kind.

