## Trial status

Protocol Version Number is 2.3 and it is approved from IRB Shaikh Zayed Hospital with ID SZMC/IRB/Internal0056/2020 on July 14th, 2020. The recruitment is in progress. It was started on July 30, 2020, and the estimated trial completion date is February 15, 2022.

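### Staff are to counsel participants on the study's advantages and beneficial outcomes while benefit is unproven, which adds to expectation bias in symptom time for the two arms that can recognise active treatment (B and C versus X)

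*Protocol article*

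**What the plan says.** Two sections of the protocol article direct what participants are told.

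- Plans to promote participant retention (item 18b): all participants "will be guided about the study conduction and its beneficial outcomes".
- Strategies to improve adherence (item 11c): "participants will be counselled about the advantages of this study".

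The abstract's discussion states benefit only as a hypothesis: "This combination is hypothesized to improve various parameters". Trial status reports that "The recruitment is in progress".

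On formulations, the intervention description (item 11a) gives arm A a capsule, arm B a syrup and arm C a spray, all active. For control: "Arm X will be receiving a placebo of empty capsule three times a day". No placebo syrup or spray is described. The blinding section (item 17a) nevertheless says that participants are blinded by means of the placebo group, that drug and placebo are alike in appearance, and that blinded clinicians assess clinical outcome.

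Time to alleviation of symptoms is one of three primary outcomes and is the endpoint named for sample size re-estimation (item 14). Under item 12 it "will be measured as the number of days the patient remained symptomatic". Item 18a has symptoms evaluated daily.

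**The concern.** A retention or adherence message that speaks of advantages and beneficial outcomes goes beyond what is known while the trial is still testing for benefit. If staff deliver it as a statement about treatment, it raises expectation.

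Expectation matters to a comparison when it differs between arms. Here it can differ, because participants in B and C can infer from the form of their treatment that they are on iodine, while capsule takers cannot tell A from X by form. The outcome most open to this is symptom duration, which depends in practice on what participants say about how they feel. A shorter reported symptomatic period in B or C than in X could then arise partly from expectation and be read as efficacy.

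**Working it through.** **1. The message against the state of knowledge.** Items 18b and 11c speak of beneficial outcomes and advantages. The abstract treats improvement as a hypothesis, and recruitment is not finished. No section shown qualifies the message, for example by asking staff to say that benefit is uncertain.

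**2. Which comparisons are exposed.** The plan's only relevant figure is the sample size: 4 arms × 50 = 200, which agrees with item 14.

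| Comparison | Forms | Recognisable by form? |
|---|---|---|
| A vs X | capsule vs capsule | no, if the capsules match |
| B vs X | syrup vs capsule | yes |
| C vs X | spray vs capsule | yes |

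B + C = 50 + 50 = 100 participants, which is 100/200 = 50% of all randomized and 100/150 = 67% of those on active treatment. The look-alike statement in item 17a can hold only for capsule against capsule.

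**3. Which outcomes are exposed.** RT-PCR result, HRCT score and death do not rest on the participant's account. Symptom duration largely does. The article does not state outright that symptoms are self-reported, but daily symptom evaluation and the closed-ended questionnaires named in the abstract imply it.

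**4. Sensitivity, not an estimate.** The document gives no effect size, SD or event rate, so the size of any expectation shift is an assumption. Take B or C against X, 50 per arm, no true effect, two-sided alpha 0.05 (the article gives 0.05 without sidedness). The chance of a significant result is

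P = Φ(δ − 1.96) + Φ(−δ − 1.96).

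For a difference in means with shift d in SD units, δ = d / √(2/50) = 5d. For a hazard ratio with 100 events (every participant in the pair resolves; Schoenfeld approximation), δ = √(100/4) × ln HR = 5 ln HR.

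| Assumed shift d (SD) | δ | P |
|---|---|---|
| 0 | 0 | 0.05 |
| 0.1 | 0.5 | 0.08 |
| 0.2 | 1.0 | 0.17 |
| 0.3 | 1.5 | 0.32 |
| 0.5 | 2.5 | 0.71 |

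| Assumed spurious HR | δ | P |
|---|---|---|
| 1.1 | 0.48 | 0.08 |
| 1.2 | 0.91 | 0.15 |
| 1.3 | 1.31 | 0.26 |
| 1.5 | 2.03 | 0.53 |

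With 50 per arm, a modest reporting shift is enough to inflate the error rate. The tables cover expectation from any source. They do not isolate the part due to the two sentences.

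**The case against.** The strongest case on the other side has five parts.

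- **The wording is about the study, not iodine.** Neither sentence tells staff to say that the drug works. A reader might infer an instruction to promise treatment benefit and safety, but the document does not support that. The advantages may be those of taking part, and the reference to safety in item 18b may mean that safety will be protected. This stands. What remains is that the wording is loose enough to be delivered either way.
- **The message is the same in every arm.** This stands, and it confines the point to B and C against X. Even there, participants must know or guess that the control is capsule-only, and the article does not say what they are told about the other arms.
- **Outcome assessors are blinded.** This helps, but a blinded clinician asking about symptoms still depends on the answers of a participant who may know the treatment.
- **The root defect is the missing placebo syrup and spray.** This stands. The counselling aggravates that gap, and rewording leaves B and C as recognisable as before.
- **The consent form and staff materials are not shown.** They may convey uncertainty properly, since item 26a says the procedure is explained in detail. That limits confidence but does not change what items 11c and 18b state.

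Two further readings should be resisted. A reader might take "as this is the first trial of its kind" in item 21b as the article's admission that benefit is unknown. That sentence explains why no stopping rules were set for the primary endpoint, and the abstract's hypothesis statement is the apt source. A reader might also put a number on the bias: shortening symptoms by 0.5 to 1 day on a median of 7 to 10 days gives, for exponential times, hazard ratios from 10/9.5 = 1.05 to 7/6 = 1.17, and with 100 events a false-positive chance of about 6% to 12%. The shift and the medians are both assumed, and exponential times fit poorly because item 12 counts from symptom onset. The figure would also cover the whole expectation effect rather than the part these sentences add.

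**Conclusion.** The point holds as a minor, cheaply corrected one. Two sections direct counselling on advantages and beneficial outcomes while benefit is only hypothesized, and nothing shown prevents this being heard as a promise of treatment benefit. It can bias B versus X and C versus X, chiefly on time to alleviation of symptoms, because those participants can recognise active treatment by its form. A versus X is not affected if the capsules match, and RT-PCR, HRCT score and mortality are far less exposed.

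The size cannot be derived from the document. The conclusion rests on two assumptions: that symptom duration depends on participants' reports, and that participants in B and C can work out that the placebo is a capsule.

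**What to change.** Replace the sentences in items 11c and 18b with one neutral script used in all arms: benefit is unknown, risks are being studied and monitored, and complete daily symptom reporting matters.

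Reconcile the blinding statement in item 17a with the formulations in item 11a, and acknowledge that B and C versus X are not masked by form for the symptom endpoint.

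The cost is rewording two sentences, the blinding statement and any matching staff material. Because recruitment was in progress, the change would protect only participants counselled after it. It reduces expectation bias in B and C but does not remove it, since those arms stay recognisable.

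### Three sections give conflicting ends of observation, and one of them, read literally, would let RT-PCR clearance end symptom follow-up

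*Protocol article*

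**What the plan says.** Four parts of the protocol article bear on how long a patient is observed.

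- **Retention and follow-up {18b}** runs the study until patients, in hospital or in home quarantine, "test negative for SARS-CoV-2 RNA in two consecutive nasopharyngeal swabs done using RT-PCR". It sets no symptom condition. It adds: "All the data will be collected while the patient is already admitted in the hospital except 30-day mortality". The later telephone contact is described for mortality.
- **Outcomes {12}** schedules RT-PCR on day 0 and "then after every 4th day for 12 days or till the symptoms are resolved and RT-PCR gets negative". HRCT has its own end: "starting from day 0 followed by every fourth day till patients’ PCR become negative". The symptom outcome is "the difference between onset of COVID-19 symptoms to complete resolution".
- **Intervention description {11a}** gives study product "for a maximum of 14 days or when the patient is fully recovered".
- **Outcome collection {18a}** says "COVID-19 symptoms evaluation will be done on daily basis to access the time taken for the alleviation of symptoms", with no last day. Section {33} likewise plans daily clinical evaluation without an end.

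Sample size {14}, in the context of re-estimation, states: "Time taken for the elevation of the symptoms will be considered as relevant endpoint (RE"; its wording evidently means alleviation. Table 1 assigns this outcome a Cox model.

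**The concern.** The sections do not agree on when observation of a patient ends, and the symptom record has no end of its own. The sentence in {18b} is the only one that says how long the study as a whole runs for a patient, and it depends on virology alone. If site staff follow it, one primary outcome decides how long another is watched.

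A Cox model needs censoring that carries no information about the event. The objectives expect iodine to improve both viral clearance and symptoms, and the two times are plausibly correlated. Follow-up that stopped at clearance would be shorter in an arm that clears faster. The patients removed early would tend to be those about to recover, so the patients left at risk would look slower than the arm really is. Resolution dates would also be lost, in an endpoint used for sample size and with only 50 patients per arm.

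**Working it through.** The 50 per arm is described as arbitrary and the follow-up rule is not a calculated figure, so there is no plan figure to reproduce. The check has four steps.

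**1. The rules side by side**

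| Section | What it governs | Stated end |
|---|---|---|
| {18b} | the study for a patient | second consecutive negative swab |
| {12} | RT-PCR swabs | 12 days, or symptoms resolved and RT-PCR negative |
| {12} | HRCT (at most 4) | RT-PCR negative |
| {11a} | study product | 14 days at most, or full recovery |
| {18a}, {33} | daily symptom or clinical evaluation | none |

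**2. Timing on the stated swab days (0, 4, 8, 12)**

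- *Negative on days 4 and 8, still symptomatic.* The {18b} end is met on day 4 + 4 = 8. Under {12} swabs may run 12 − 8 = 4 days longer. Under {11a} dosing may run up to 14 − 8 = 6 days longer. The symptom endpoint has not yet occurred.
- *First negative on day 12.* The second negative needs a swab on day 12 + 4 = 16, which is 4 days past the {12} schedule and 2 days past the {11a} maximum.

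So {18b} and {12} cannot both hold for every patient.

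**3. What happens if {18b} alone governed (illustration; every input is assumed)**

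Log-normal times with SD 0.5 on the log scale. Median symptom time after randomisation 6–12 days, median control clearance 5 or 8 days. Treatment multiplies clearance time by 0.6 and has no effect on symptoms. Clearance is rounded up to the 4-day swab grid, follow-up ends one swab later (cap day 28), and swabs may continue past day 12. There are 200,000 simulated patients per scenario. Results at correlation 0.5:

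| Median symptom / control clearance (days) | Cut off, control | Cut off, treated | Resolution hazard ratio (truth 1.00) |
|---|---|---|---|
| 6 / 5 | 8% | 19% | 0.98 |
| 6 / 8 | 2% | 9% | 0.98 |
| 8 / 5 | 23% | 40% | 0.94 |
| 8 / 8 | 10% | 24% | 0.97 |
| 10 / 5 | 40% | 59% | 0.90 |
| 10 / 8 | 21% | 42% | 0.91 |
| 12 / 5 | 56% | 73% | 0.86 |
| 12 / 8 | 35% | 58% | 0.88 |

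At zero correlation 7–55% of control and 14–70% of treated patients are cut off, and the hazard ratio stays at 0.99–1.01. For comparison, 8–50% are unresolved at a fixed day 12 under the same inputs, but that limit is the same for every patient and does not depend on RT-PCR.

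A second simulation assumed symptom medians of 7–10 days, clearance medians of 6–8 days and clearance 1.5-fold faster on iodine. It left 4–37% of resolutions unobserved in control and 12–50% on iodine. The hazard ratio was essentially unchanged at zero correlation and 3–10% lower at 0.6.

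**4. Size against the trial**

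*Bias.* In the most extreme row, observed resolutions with 50 per arm are 50 × 0.44 + 50 × 0.27 = 35.5. The standard error of the log hazard ratio is about 2/√35.5 = 0.34. The shift is ln 0.86 = −0.15, so 0.15/0.34 ≈ 0.45 standard errors.

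*Information.* One arm against placebo, two-sided 0.05, assumed hazard ratio 1.75: power = Φ(½ √events × ln 1.75 − 1.96), with ln 1.75 = 0.56.

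- All 100 resolutions seen: Φ(0.84) = 80%.
- Row 6 / 8: 50 × 0.98 + 50 × 0.91 = 94.5 events, Φ(0.76) = 78%.
- Row 8 / 5: 50 × 0.77 + 50 × 0.60 = 68.5 events, Φ(0.36) = 64%.
- Row 12 / 5: 35.5 events, Φ(−0.29) = 38%.

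These event counts come from the no-effect runs, so the power figures are for orientation only.

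**The case against.** The strongest reply is that a reader might infer that RT-PCR does cut off the symptom endpoint and that resolution dates are never recorded in such patients. The documents do not say so. No sentence stops symptom recording at the second negative swab. Sections {18a} and {33} plan daily evaluation with no RT-PCR stop, and {12} defines the outcome to complete resolution. Section {11a} allows dosing to full recovery, and {11c} has health professionals giving the drug under direct observation, so a patient still being dosed could well have the date recorded. The {18b} sentence sits under retention and may have been meant as a commitment on virology. All of that stands, and it limits the point to what the text permits.

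A reader might also infer a spurious benefit for iodine. The simulations show the opposite: the shift is nil without correlation and otherwise runs against iodine. When the second set of assumptions was repeated with 50 per arm, false wins for iodine were 0–2% against a nominal one-sided 2.5%.

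Calling symptom time the lead endpoint is open to dispute as well: {12} lists three primary outcomes and {33} refers to RT-PCR negativity as the primary end point. It is nonetheless the one {14} singles out for sample size.

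Finally, an article may leave the exact end of symptom follow-up to a fuller document. That answers silence. It does not answer stated rules that contradict one another, one of which gives a worse result if it is followed.

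**Conclusion.** The point holds as a contradiction between {11a}, {12} and {18b}, combined with a symptom record that has no end of its own. Read literally, {18b} permits symptom follow-up to end as early as day 8 in a patient who is still symptomatic, and so permits censoring by another outcome that treatment may affect. It also calls for a day-16 swab in a patient first negative on day 12, which {12} does not schedule.

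The bias would be modest: none if clearance and symptom times are independent, roughly 2–14% off the resolution hazard ratio at correlations of 0.5–0.6, and against iodine. The loss of observed resolutions is the more certain cost, because it occurs with or without correlation. Its size depends on assumed recovery and clearance times, none of which the protocol gives, and on {18b} being the rule that sites follow. Severity: should fix.

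**What to change.** Reconcile the sections, and give symptom follow-up its own end in {18b}, {12} and {18a}. Suggested text: 'Daily symptom status is recorded until complete resolution or day 30 after randomisation, whichever comes first, regardless of RT-PCR results. Patients unresolved at that day are censored there.' Day 30 is an example, chosen because mortality is already assessed then; another fixed day would serve. State separately when swabbing ends, so that the two-negative condition and the 12-day schedule agree. The treatment period in {11a} needs only to be made consistent with the other sections; no change to it is proposed here.

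The cost is a short text amendment and brief telephone symptom checks for patients still symptomatic after clearance. Those calls go beyond the mortality contact already planned. Depending on recovery times, they could involve a substantial share of patients rather than a few.
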